##### Treatment Outcomes

For exploratory purposes, we will examine group differences in treatment outcomes. Group differences in anxiety and depression will be analyzed for both dichotomous (diagnosis) and continuous (symptom severity) measures. For each diagnosis (presence vs absence), chi-square tests will be performed comparing the number of youth meeting criteria for diagnosis at pre versus post, pre versus follow-up 1, and pre versus follow-up 2. For each of the continuous measures of symptom severity, following the recommended approach for trials with pre, post, and follow-up measures [115], a repeated measures multivariate analysis of the covariant will be performed in which the between factor is group (app vs no-app) and the within factor is time (pre, post, follow-up 1, follow-up 2), to compare group and time effects and interactions between group and time, using the pretreatment value as a covariate. Where significant effects are found, simple contrasts will be conducted to ascertain where the significant differences lie. Group differences in maladaptive cognitions (overall score) and quality of life (overall score), will be analyzed in the same way. Effect sizes will be calculated comparing the effects of app vs no-app on each of the outcomes. Analyses will also be performed to establish clinical significance and the reliable change index [116]. Subgroup analyses will explore differences in the app’s impact on treatment outcomes as a function of test site and gender.

If the analyses reveal significant group differences in treatment outcomes, additional exploratory analyses will be performed to aid interpretation of the data. To explore whether better homework completion (greater quantity and/or quality) or something unique about the mobile technology is most likely responsible for group differences in treatment outcomes, we will examine associations between homework completion and treatment outcomes separately for the 2 groups. Mobile devices may increase patient engagement and empowerment [1,117] and reduce concern about the perceived stigma associated with receiving treatment [118], resulting in beneficial effects on treatment that are independent of homework completion. Accordingly, regression analyses (ordinary least squares, logistic) would be performed to predict each of the dichotomous (diagnosis) and continuous (symptom severity) outcomes at posttreatment, follow-up 1, and follow-up 2 from measures of homework completion, controlling for the pretreatment value of the outcomes. A finding of group differences in the strength of associations between homework completion and treatment outcomes would suggest that an improvement in homework completion is not the only mediator of app effects on treatment outcome.

Finally, if treatment outcomes are better for the app compared with the no-app group, exploratory mediation analyses will be performed for the app group to assess whether homework completion (quantity, quality) affects treatment outcomes indirectly through support for learning (ratings of how much the app supports access to assignments, memory and understanding of lessons, motivation to practice, coaching and suggestions, self-monitoring of symptoms and changes, review of homework). To test for mediation, we will perform tests of indirect effects using a regression-based path-analytic approach [119,120].

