#### Sample

An independent sample will be recruited consisting of 20 youth in CBT and their therapist **s**, distributed approximately equally across 5 clinics that provide CBT treatment for youth with anxiety and/or depression. Participants will receive a CAD$30 gift card as an honorarium. Youth will be recruited from among 12- to 18-year olds with a primary diagnosis of anxiety (general anxiety disorder, separation anxiety, social anxiety, panic disorder) and/or depression (major depressive disorder, dysthymic disorder). Informed consent will be obtained from youth, their primary caregiver, and their therapist. Youth receiving medication will be included if they were on a stable dose for approximately 6 weeks prior to and throughout participation. Those with a primary diagnosis of obsessive-compulsive disorder or post-traumatic stress disorder, and those with comorbid psychosis or substance dependence will be excluded because they require different CBT strategies from those that are the focus of this research. Those who are behind by 2 or more school grades or have a profound learning disability will be excluded, given the cognitive and verbal nature of CBT. Substance use and mild learning difficulties will not be exclusion criteria. Based on intake rates of approximately 1 per week at each clinic, we expect to recruit 5 youth per week. Interest in trying the app is expected to be high. Two evaluation cycles, each with up to 10 youth and their therapists, should be sufficient to reach saturation [82], but the sample size allows for an additional cycle if needed. Youth will be given the choice of receiving a smartphone to use or using their own. They will be compensated for the cost of a basic service plan (voice, text, Internet) for 12 weeks to use the app.

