#### Recruitment

Recruitment will be the same as in Phase 2. In previous work in our clinics, consent rates have been 80% or higher. Interest in using the app is expected to be high. Typically, intake at the test sites is approximately 1 per week and the wait-list period is at least 12 weeks for noncrisis patients. Therefore, based on intake and consent rates and assuming sequential recruitment, we will recruit at a rate of 5 youth per week across the 5 sites, reaching an overall sample of 100 within 6 months. Posttreatment assessments would be completed at the end of treatment (ie, 3 months later), and the follow-ups 6 and 12 months thereafter. The same inclusion and exclusion criteria apply as in Phase 2.

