#### Data Analysis

To assess the app’s effectiveness, differences between the app and no-app groups will be examined with respect to homework completion. We will also explore group differences in treatment outcomes. Although randomization will be used to mitigate group differences, potential differences between groups will be examined. If differences are found on variables that may be related to homework completion or treatment outcome (symptom severity/diagnosis, age, sex distribution, history of psychotherapy and pharmacological interventions, comorbid mental health problems, therapist), these variables will be included as covariates in the analyses. Descriptive analyses will be performed on demographic characteristics, comfort with computers, and retention rates (participants assessed at posttreatment and follow-ups). To avoid bias in parameter estimates, missing data will be handled by performing intent-to-treat analyses, in which missing values are replaced using the last observation carried forward, a method appropriate for randomized designs [114].

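### The diagnosis outcome is counted disorder by disorder although youth enter with different disorders, so absolute app effects are diluted and loss of the entry disorder is never measured

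*Protocol article*

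**What the plan says.** **Who enters.** The Phase 2 Sample section requires a "primary diagnosis of anxiety (general anxiety disorder, separation anxiety, social anxiety, panic disorder) and/or depression (major depressive disorder, dysthymic disorder"). The Phase 3 Recruitment section carries this over: "The same inclusion and exclusion criteria apply as in Phase 2". No youth must have both kinds of disorder, and none must have any particular one.

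**What is counted.** The Treatment Outcomes section announces an exploratory look at group differences in anxiety and depression, both dichotomous and continuous. For the dichotomous part it says: "For each diagnosis (presence vs absence), chi-square tests will be performed comparing the number of youth meeting criteria for diagnosis". The contrasts it then names are between time points: "at pre versus post, pre versus follow-up 1, and pre versus follow-up 2".

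**Who is analysed.** The Data Analysis section states that "missing data will be handled by performing intent-to-treat analyses, in which missing values are replaced using the last observation carried forward". Neither section limits a diagnosis to youth who had it at pretreatment, and neither defines loss of the entry diagnosis as an outcome.

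**What data exist.** The Phase 3 Measures section schedules the ADIS interview at pretreatment, posttreatment and both follow-ups.

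**The concern.** A youth who never had panic disorder is free of it at pretreatment and can afterwards only stay free of it or become a new case. In a comparison of the arms at posttreatment, that youth counts the same as one who had the disorder and lost it. Each disorder-specific comparison thus carries youth who had nothing to lose, and the more varied the entry diagnoses, the more of them there are.

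Two things are at stake. The absolute difference for each disorder is smaller than the effect on the youth treated for it, with few events behind it. And no dichotomous result answers the plain clinical question of whether youth lose the disorder they came with.

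The outcome is exploratory, but it has consequences inside the plan. The regressions relating homework to outcome run only if treatment outcomes differ significantly between groups, and the mediation analyses only if they are better with the app. A weak dichotomous outcome makes one route to those analyses less likely to open.

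**Working it through.** The protocol gives no expected rate or power for the diagnosis outcome, so there is no figure of its own to reproduce. Its one power statement (0.84 with 35 per group) concerns homework completion.

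**Inputs**
- 50 per arm: 100 youth, 10 per group at each of 5 sites (Sample Size and Power). Under the stated intent-to-treat rule with values carried forward, all 50 stay in the analysis.
- Persistence among affected youth without the app: 35%. This is an assumption, set just above the Background section's statement that anxiety diagnoses remained in more than one-third after CBT.
- Persistence with the app: 20%. This is an assumption with no source in the document.
- Share π with a given disorder at pretreatment: not given, so a range is shown.
- New cases: assumed none.

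**Formulas**
- Rate in all youth = π × persistence, so the difference = π × (0.35 − 0.20).
- z = difference / √(p₁q₁/50 + p₂q₂/50).
- Restricted to baseline cases: z = 0.15 / √((0.2275 + 0.16)/(50π)), where 0.2275 = 0.35 × 0.65 and 0.16 = 0.20 × 0.80.
- Information ratio = (z restricted / z all youth)².

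**Entry-diagnosis outcome, all 50 per arm:** 0.15 / √(0.3875/50) = 0.15/0.0880 = 1.70.

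| π | Rates, all youth | Difference | z, all youth | z, baseline cases only | Information ratio |
|---|---|---|---|---|---|
| 80% | 28.0% vs 16.0% | 12.0 points | 1.46 | 1.52 (40 per arm) | 1.1 |
| 50% | 17.5% vs 10.0% | 7.5 points | 1.10 | 1.20 (25 per arm) | 1.2 |
| 30% | 10.5% vs 6.0% | 4.5 points | 0.82 | 0.93 (15 per arm) | 1.3 |
| 15% | 5.25% vs 3.0% | 2.3 points | 0.57 | 0.66 (7.5 per arm) | 1.4 |

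At 30% prevalence the expected cases are 50 × 0.105 = 5.25 and 50 × 0.06 = 3.

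**Splitting the loss at 30%.** The entry-diagnosis outcome carries (1.70/0.82)² = 4.3 times the information of the all-youth count. Of this, 1.3 comes from the denominator. The remaining factor, 50/15 = 3.3, comes from having only 15 affected youth per arm instead of 50. Pooling supplies most of the gain.

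**Check with other assumed rates.** With persistence of 50% versus 25%, two-sided α = .05 and 50 per arm, power is 0.74 on an outcome that all youth can reach. Per diagnosis over all youth it is 0.36 at π = 50% and 0.22 at π = 30%; restricted to baseline cases it is 0.44 and 0.29. The pattern is the same.

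**The case against.** **The denominator is inferred.** A condensed article may leave denominators to a fuller document, and no sentence says that all youth are counted. This has some weight. But the section does fix the unit (each diagnosis), the count (youth meeting criteria) and the time points, under intent-to-treat. Followed as written, it gives the diluted comparison, and it names no common outcome.

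**The tests as worded compare times, not arms.** In a pre versus post count, a never-affected youth is absent both times and adds nothing to the number who change. This stands: the z values above describe an app versus no-app test, which the chi-square sentence does not specify, although the paragraph's stated aim is group differences. Correcting the contrast would still leave the denominator problem.

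**Stronger readings a reader might infer.**
- *That the denominator alone costs a fourfold loss of information.* It does not; most of that loss is from fewer affected youth. With no new cases the risk ratio is not diluted at all.
- *That there are 18 comparisons* (six disorders × three times). This is one reading. The paragraph speaks of anxiety and depression, and two categories would give 2 × 3 = 6 comparisons, higher prevalence and less dilution, as in the 80% row.
- *That the symptom scales and the clinical-significance analysis share the fault.* The document does not support this. The scales are analysed "using the pretreatment value as a covariate", youth without a diagnosis may still have raised scores, and several measures are not tied to one disorder. For the rest, "Analyses will also be performed to establish clinical significance and the reliable change index" gives no population and rests on a cited source that is not shown.

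**A single primary diagnosis may not exist.** Eligibility allows anxiety and depression together, and the article describes no ranking by the ADIS. This stands, and it shapes the fix.

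**Conclusion.** The point holds for the dichotomous diagnosis outcome only. As written, it is spread over disorders that many youth may not have had at entry, and no outcome records loss of the entry disorder. In a comparison of the arms, with no new cases, the absolute effect for each disorder is π times the effect among affected youth. In the illustration, 15 points fall to 7.5, 4.5 or 2.3 points at 50%, 30% or 15% prevalence.

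The size rests on assumed persistence, assumed prevalence and no new cases; the direction needs only that some youth lack the disorder and that the app adds no effect through new cases. Even the pooled outcome reaches only z = 1.70 here, so it improves the estimate without making the trial well powered for it.

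A reader might infer that the trial's main conclusion is at risk. It is not: treatment outcomes are exploratory, and the homework hypothesis and its stated power do not depend on this count. The change is worth making because it is cheap and gives the diagnosis result a clear meaning.

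**What to change.** In the Treatment Outcomes section, make the main dichotomous treatment outcome: no longer meeting ADIS criteria for the qualifying anxiety and/or depressive diagnosis or diagnoses held at pretreatment. Compare it app versus no-app at posttreatment, follow-up 1 and follow-up 2. Require youth who enter with both an anxiety and a depressive diagnosis to lose both, so that nobody needs a single ranked diagnosis and every randomised youth can be scored. Fix the list of qualifying diagnoses for each youth from the pretreatment assessment, which already precedes randomisation.

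Report each disorder separately only among youth who had it at pretreatment, as descriptive results.

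The cost is analysis wording: the ADIS is already scheduled at all four time points. The downside is small: there is no formal test for each separate disorder. Requiring loss of both diagnoses may also raise persistence above the rates assumed here for youth who enter with both.

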## Introduction

### Background

Mobile technology has the potential to make mental health treatments more effective and efficient in alleviating mental health problems [1-4]. In particular, youth anxiety and depressive disorders may benefit from the use of mobile technology to improve treatment. The incidence of these disorders peaks during adolescence [5-7], putting them among the top 5 causes of illness and disability in the world [8]. Their persistence into adulthood often takes a great toll on daily functioning in social, work, and family contexts, reducing health-related quality of life [9,10], and placing a heavy financial burden on society and health care services [11,12]. Given the long-term impact of these disorders on individuals, families, and society and their high economic burden, increasing the effectiveness of early treatment could have a significant impact. Cognitive behavior therapy (CBT) is the established efficacious treatment for anxiety and depressive disorders. It has been shown to be an effective treatment for anxiety and depression in children and youth across a wide range of ages [13-19] and using various modes of delivery (eg, individual and group) [20,21]. Notwithstanding CBT’s effectiveness, many individuals are not successfully treated and continue to have significant symptoms [22-24]. For example, in a systematic review of CBT for anxiety in young people, anxiety diagnoses were still present at the end of treatment in more than one-third of participants [23]. Increasing the success of CBT in treating adolescents would result in a lower rate of relapse. A promising target for increasing the success of CBT is the homework component.

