At pre, post, and each follow-up, treatment outcomes will be assessed. Anxiety and depression will be assessed using the same instruments as in Phase 2: the Achenbach Scales, which assess general symptomatology as reflected in internalizing problems, and externalizing problems, which often co-occur with anxiety and depression [105], the MASC-2, the CDI-2, and the ADIS. Other outcomes also will be assessed. Maladaptive cognitions will be assessed using the Children’s Automatic Thoughts Scale [106], in which youth rate the frequency over the past week of a set of 40 self-statements describing negative thoughts about physical threats, social threats, personal failure, and hostile intent. Quality of life will be assessed by the Pediatric Quality of Life Inventory [107,108], in which youth rate 23 self-statements assessing physical, emotional, social, and school functioning.

At posttreatment, a usability evaluation will be conducted with the app group (youth and therapists) following completion of the posttreatment assessment, using the same protocol as in Phase 2. To examine differences in client satisfaction between the app and no-app groups, will be assessed posttreatment (following the usability evaluation in the app group) via the Client Satisfaction Questionnaire (CSQ [109,110]), an 8-item global measure of satisfaction with service comprised of statements phrased as questions to be answered on a 4-point scale ranging from 1 (poor) to 4 (excellent). The CSQ is a well-established measure with good psychometric properties [110] that has been used in numerous studies with diverse patient samples, including children and adolescents in CBT [111,112]. Treatment fidelity will be assessed by an integrity-to-protocol checklist [113], which therapists will complete after each session. The checklist yields a proportion score reflecting the rate of adherence to the CBT treatment manual. Finally, health economic cost data will be obtained to assess cost-effectiveness of the app. Cost data will consist of technology costs, including detailed micro costing of the app program (eg, program costs, smartphone-related costs, server costs, maintenance), and the cost of time and other resources needed to integrate the app into routine clinical practice by therapists and clinics.

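### For the exploratory diagnosis outcome, the plan aims at group differences but names only chi-square tests of pre against later counts, and no app versus no-app test

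*Protocol article*

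**What the plan says.** All of this is in the Phase 3 part of the protocol article.

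- **Status.** Treatment Outcomes opens with "For exploratory purposes, we will examine group differences in treatment outcomes".
- **Aim.** The next sentence reads "Group differences in anxiety and depression will be analyzed for both dichotomous (diagnosis) and continuous (symptom severity) measures".
- **Named test for diagnosis.** For each diagnosis, present or absent, "chi-square tests will be performed comparing the number of youth meeting criteria for diagnosis at pre versus post, pre versus follow-up 1", and then pre against follow-up 2.
- **Named model for severity.** The continuous measures get a repeated measures analysis in which "the between factor is group (app vs no-app) and the within factor is time (pre, post, follow-up 1, follow-up 2", with the group-by-time interaction.
- **Effect sizes.** Later in the section: "Effect sizes will be calculated comparing the effects of app vs no-app on each of the outcomes". No measure is named for diagnosis.
- **Data structure.** Measures states "At pre, post, and each follow-up, treatment outcomes will be assessed", so each youth contributes to both counts in every contrast.
- **Gate.** "If the analyses reveal significant group differences in treatment outcomes, additional exploratory analyses will be performed".

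**The concern.** The aim is a comparison between arms and the named contrast is a comparison over time. According to Study Design, both arms receive 12 weeks of manualized CBT and differ only in how homework is delivered. Diagnoses are expected to fall in both arms whether or not the app helps. A significant pre-post chi-square would therefore be evidence of change under treatment, not of an app effect, and it could be misread as one.

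The gate adds a practical consequence. Further analyses depend on significant group differences in treatment outcomes, and for diagnosis no named test can establish such a difference.

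A second, smaller fault is that a chi-square on two sets of counts assumes independent observations. Here the same youths are counted at both times.

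**Working it through.** The article gives no sample size, power or rate for the diagnosis outcome, so there is no stated figure to reproduce. The check has three parts.

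**1. Does any named test supply the group contrast?**

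- The chi-square names time points only.
- The continuous measures, in the same paragraph, name group, time and their interaction. The article does state the group factor where it uses one.
- The logistic regression later in the section predicts diagnosis from homework completion, and runs only after group differences have been found. It does not test app against no-app.
- Reading chi-square loosely as McNemar's test would repair the pairing but not the missing group contrast.

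**2. What does the written test show when the app does nothing?**

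Inputs:
- 50 per arm (Sample Size and Power: 10 per group at each of 5 sites).
- 40% of youths with the diagnosis at pre still have it at post, the same in both arms, with no new cases. This is an assumption. Background cites a review in which "anxiety diagnoses were still present at the end of treatment in more than one-third of participants".
- Prevalence at pre of each diagnosis is not given. The test is run per diagnosis in a sample with mixed anxiety and depressive diagnoses, so a range is shown.

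With a cases at pre and b at post among n = 50, Pearson chi-square = 2n[a(n − b) − b(n − a)]² / [n²(a + b)(2n − a − b)].

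| Pre prevalence | Pre count | Post count | Chi-square within arm | p |
|---|---|---|---|---|
| 20% | 10/50 | 4/50 | 2.99 | 0.08 |
| 30% | 15/50 | 6/50 | 4.88 | 0.03 |
| 40% | 20/50 | 8/50 | 7.14 | 0.008 |
| 60% | 30/50 | 12/50 | 13.3 | 0.0003 |
| 100% | 50/50 | 20/50 | 42.9 | 6 × 10⁻¹¹ |

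First row in full: 100 × (10 × 46 − 4 × 40)² / (2500 × 14 × 86) = 100 × 300² / 3,010,000 = 2.99.

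In every row the two arms have the same post count, so the between-arm chi-square at post is 0. The article does not say whether the test is run within each arm or on both arms pooled. Pooling identical arms doubles the statistic, so even the first row becomes 5.98, above the 5% critical value of 3.84.

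A simulation (20,000 runs, 50 per arm, 35% persistence in both arms, 5% new onset, pre prevalence 40% to 100%) agrees. The pre-post test is significant in 79% to 100% of trials within an arm and in 99% to 100% pooled. A between-arm test at post is significant in about 5%, its nominal level.

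**3. What does ignoring the pairing do?**

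If prevalence p does not change and the within-youth correlation of the two binary values is φ, the true variance of the difference is (1 − φ) times the variance that the unpaired test assumes. The true level is about P(|Z| > 1.96/√(1 − φ)). With p = 0.6 at both times:

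| Latent correlation | φ | Approximate true level | Simulated, n = 50 |
|---|---|---|---|
| 0.4 | 0.26 | 2.3% | 2.4% |
| 0.6 | 0.41 | 1.1% | 1.2% |
| 0.8 | 0.59 | 0.2% | 0.2% |

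The true level is below 5% throughout. The unpaired test loses power to detect change over time; it does not create false positives.

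**The case against.** The strongest case on the other side is one of proportion. The outcome is exploratory. The trial's hypothesis and its power statement concern homework completion, which has its own group comparison. Symptom severity, maladaptive cognitions and quality of life all have an explicit group factor, so the gate has defined tests from those outcomes, and it opens only further exploratory work. All of this stands, and it lowers the severity.

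The chi-square sentence follows directly on one about group differences, so in a condensed article it might be shorthand for comparing change between arms. That is possible, but the words name time points and no group. The article fixes a contrast here, so this is not detail left to a fuller document.

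A reader might infer more than the document supports:

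- **That app and no-app are never compared on diagnosis.** Effect sizes for app against no-app are promised for each outcome. What is missing is a named test, and a named effect measure for diagnosis.
- **That the pre-post test will be strongly significant in both arms whatever the app does.** This depends on prevalence at pre. At 20% the within-arm p is about 0.08. The value of 42.9 needs every youth to have the same specific diagnosis, which is a ceiling case.
- **That the plan would judge the app by comparing p-values between arms.** The article does not propose this.
- **That the pairing error inflates false positives.** It works in the opposite direction.

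**Conclusion.** The point holds in limited form. For diagnosis, the named test does not answer the stated aim. It measures change under CBT, cannot separate the app from the treatment that both arms receive, and leaves the gate without a test for this outcome. With no app effect, the within-arm statistic can lie anywhere from about 3.0 to 42.9, depending on how common the diagnosis is at pre. That range assumes 50 per arm, 40% persistence in both arms, no new cases and no dropout. The main conclusion does not rest on these assumptions, because it follows from the contrast itself.

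The pairing fault is real but secondary and conservative. Severity: should fix. The primary homework hypothesis is not affected.

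**What to change.** Replace the stated contrast with app versus no-app on the presence of each diagnosis at post, follow-up 1 and follow-up 2, adjusted for pretreatment diagnosis. Logistic regression at each time would do, or a GEE or mixed logistic model over the three times. Include site where counts allow. For rare diagnoses use an exact or simple two-group comparison: at 20% prevalence the illustration leaves only 4 + 4 = 8 cases at post, too few for a model with several terms.

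Report an odds ratio or risk difference with its 95% CI, which also settles the effect measure for diagnosis. State that this comparison is the one that counts towards the gate. If change within arms is reported, use McNemar's test and label it descriptive.

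The cost is a sentence or two in the analysis section, on data already planned. The authors should expect limited precision. In the simulation with persistence of 20% in the app arm and 40% in the no-app arm (assumed), 50 per arm and 5% new onset, an unadjusted between-arm test at post had power of 21% to 60% as pre prevalence rose from 40% to 100%. That is a reason to lead with the interval rather than the p-value.

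### The exploratory outcome models use the pretreatment score as both a time level and the covariate, so the group × time test does not show whether a benefit lasts

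*Protocol article*

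**What the plan says.** The model is specified in the Treatment Outcomes section of the Phase 3 data analysis. For each continuous symptom measure, "a repeated measures multivariate analysis of the covariant will be performed in which the between factor is group (app vs no-app"). Pretreatment is the first of the four occasions listed: "the within factor is time (pre, post, follow-up 1, follow-up 2"). Main effects are to be tested together with "interactions between group and time, using the pretreatment value as a covariate".

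Three further statements set the scope:

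- Significant results are followed up: "Where significant effects are found, simple contrasts will be conducted to ascertain where the significant differences lie".
- The model is reused: "Group differences in maladaptive cognitions (overall score) and quality of life (overall score), will be analyzed in the same way".
- The section is exploratory: "For exploratory purposes, we will examine group differences in treatment outcomes".

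Later in the same section, the regressions of outcome on homework completion use only posttreatment and the two follow-ups as outcomes and adjust for the pretreatment value. Those regressions do not have the overlap. Nothing else in the article takes pretreatment out of the time factor.

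**The concern.** A baseline score can serve as the first outcome occasion or as a covariate. If it is both, the model regresses baseline on itself. That level then carries no information on treatment, yet it still counts as one of four in the time-averaged group effect and as one of the times compared in the interaction.

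What is at stake is interpretation. The Study Design section schedules the follow-ups to see how the app performs both straight after treatment and later. In this model a reader would naturally look to group × time for evidence that a benefit lasts or fades, and as specified that test answers a different question. The raw group average is also not the quantity most readers would take it to be.

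**Working it through.** **Inputs from the protocol.** There are four time levels, with the pretreatment value as covariate and tests of group, time and group × time (Treatment Outcomes). Pretreatment assessment comes before randomisation (Study Design), so no true group difference is expected there. The sample size section gives 35 per group in the power calculation and 100 recruited, which is 50 per group.

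**The plan's own figure.** There is none for this model. The stated power of 0.84 concerns homework completion and is not at issue.

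**Assumptions, not in the protocol.** SD 1 at every visit, equal correlation ρ between visits (0.3, 0.5, 0.7), and a true benefit of 0.50 SD at all three later visits.

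**Step 1: adjusted group differences.** Write Y0 for pretreatment, Y1 to Y3 for the later visits and G for group:

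Yj = aj + dj·G + bj·Y0 + ej

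For j = 0 the fit is perfect with b0 = 1, so d0 = 0 and e0 = 0. The adjusted group differences are (0, d1, d2, d3).

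**Step 2: the group main effect.**

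- Four levels: (0 + d1 + d2 + d3)/4 = 3/4 × (d1 + d2 + d3)/3.
- With dj = 0.50: 1.50/4 = 0.375 SD, against 1.50/3 = 0.50 SD with three levels.
- The residual of the four-level mean is likewise 3/4 of the residual of the three-level mean, because e0 = 0. The standard error shrinks by the same factor, so t and p are identical.

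The ratio needs complete data but does not depend on ρ, sample size or time course. The Data Analysis section plans to carry the last observation forward, which would make the analysed data complete.

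**Step 3: the interaction.**

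- Four levels: the differences Yj − Y0 have group coefficients dj − 0 = dj. The multivariate test is of d1 = d2 = d3 = 0, that is, of any effect after baseline.
- Three levels: the differences Y2 − Y1 and Y3 − Y1 have group coefficients d2 − d1 and d3 − d1. The test is of d1 = d2 = d3, that is, of whether the effect is stable.

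**Step 4: simulation.** 4,000 trials per setting, no dropout, exact Wilks F for the interaction, stable 0.50 SD benefit:

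| Per arm | ρ | Group estimate, 4 / 3 levels | Group × time rejected, 4 / 3 levels | Group effect rejected, 4 / 3 levels |
|---|---|---|---|---|
| 35 | 0.3 | 0.373 / 0.497 | 0.714 / 0.051 | 0.864 / 0.864 |
| 35 | 0.5 | 0.373 / 0.497 | 0.745 / 0.052 | 0.885 / 0.885 |
| 35 | 0.7 | 0.376 / 0.502 | 0.874 / 0.053 | 0.954 / 0.954 |
| 50 | 0.3 | 0.374 / 0.499 | 0.888 / 0.049 | 0.959 / 0.959 |
| 50 | 0.5 | 0.376 / 0.501 | 0.897 / 0.049 | 0.963 / 0.963 |
| 50 | 0.7 | 0.376 / 0.502 | 0.966 / 0.052 | 0.992 / 0.992 |

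The ratio of the two estimates was 0.750 in every simulated trial. At 50 per arm and ρ = 0.5, the mean adjusted differences by visit were 0.00, 0.503, 0.500 and 0.500.

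Two further runs, also at 50 per arm and ρ = 0.5:

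- **No effect:** group × time was rejected in 0.046 (four levels) and 0.047 (three levels) of trials; the group effect in 0.048 under both.
- **Fading benefit (0.5, 0.4, 0.3):** the group estimate was 0.298 against 0.397, and the interaction was rejected in 0.752 against 0.121. The four-level interaction is thus significant less often for a benefit that fades (0.752) than for one that does not (0.897). It responds mainly to the size of the effect, not to its change over time.

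**The case against.** The strongest reply is that little of substance is harmed, and much of it stands.

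- **Exploratory status.** The trial's hypothesis concerns homework completion, which is analysed over early, middle and late treatment without this covariate. That is correct, and it limits the weight of the point.
- **Validity of the tests.** A reader might infer lost power or extra false positives. Neither follows: the group test is identical in both versions, and the multivariate interaction rejects at about 5% when there is no effect.
- **Effect sizes.** A reader might infer that every reported effect is a quarter too small. The protocol does not support this. It does not say how effect sizes will be derived, and those based on F, t or the model's own residual SD are unchanged, as are adjusted differences at single visits. Only the raw four-level average, or that average divided by a single-visit SD, is reduced.
- **Meaning of the interaction.** With a baseline level in the model, a significant interaction reflects a real effect, and the protocol never says that it tests durability. A reader might infer that a stable benefit would be reported as changing. That is a risk of misreading and not a certainty, since the planned follow-up contrasts could show zero at pretreatment and a flat benefit afterwards.
- **Loose wording.** The coherent regressions later in the section make a slip in drafting plausible, and the source cited for the approach is not at hand. Still, an analyst following the sentence would include pretreatment in both roles, and the difference-based multivariate interaction test would run without warning.

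What remains is an explicit double use of baseline in one sentence, with two quantities that do not mean what they appear to mean.

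**Conclusion.** The point holds, at moderate weight. With complete data, the raw time-averaged group difference is exactly 3/4 of the mean difference after baseline; this is algebra and needs no further assumption. The group × time test becomes a test of any effect after baseline and cannot show whether the effect changes from posttreatment to 12 months.

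The 71% to 97% rejection rate, against about 5% with three levels, is an illustration. It rests on an assumed stable 0.5 SD benefit, equal correlations of 0.3 to 0.7, 35 to 50 per arm and no dropout. The protocol gives neither an effect size nor a correlation for these outcomes.

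The overlap affects every continuous symptom measure, maladaptive cognitions and quality of life. It does not affect the conclusion on whether the group main effect is significant, the homework analysis or the sample size.

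**What to change.** Define the within factor as time with three levels (posttreatment, follow-up 1, follow-up 2) and keep the pretreatment value as covariate, in line with the regressions later in the section. Group is then the mean effect after treatment, and group × time tests whether it lasts.

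The alternative is to keep pretreatment as a time level and drop the covariate. Group × time would then carry the treatment effect, the group main effect would still average in a visit with no expected difference, and durability would need a separate contrast among the three later visits.

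Either way, state which estimate the effect sizes come from. A mixed model is optional and not needed to resolve the overlap. The cost is a reworded sentence, with no new data, visits or participants.
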